## K. Interim Analyses

For each specific aim, we have developed an interim analysis plan to monitor the endpoints over the course of the study. For specific aims 1 and 3, which monitor primary (asthma and recurrent wheeze) and secondary (e.g., eczema, LRI) outcomes in the infants, this sequential monitoring plan consists of three interim analyses (conducted at year 3 month 5, year 4 month 5, and year 5 month 5 and a final analysis at the end of the study, when the three-year follow-up has been completed on all subjects. For specific aims 2 and 4, which involve outcomes monitored at delivery (i.e., circulating 25(OH)D levels in maternal and cord blood), there will be two interim looks and a final analysis (year 2 month 5, year 3 month 5, and year 4 month 5, respectively).

For maximum flexibility in the analysis, we will use a Lan-Demets alpha spending function with O'Brien-Fleming bounds. The software program LANDEM (<http://www.biostat.wisc.edu/landemets/>) was used to calculate the crossing boundaries, which, for the first and third specific aims are  $|z|=4.3329$ ,  $2.9631$ ,  $2.3590$ , and  $2.0141$ , at the first, second, third and final analyses, respectively. For the second and fourth specific aim, with 3 looks in total, the crossing boundaries are  $|z|=3.7103$ ,  $2.5114$ , and  $1.993$  at the first, second looks and final analysis, respectively. While the looks in the interim analyses have been predetermined, the Lan-DeMets procedure provides a spending function approach which does not require pre-specification of the frequency or timing of interim looks. This can be advantageous if the timing of data collection varies or if the need for more frequent monitoring arises. Conservative O'Brien-Fleming bounds are used to preserve most of the type-I error for the final analysis. For all specific aims, the hypothesis tests are conducted with two-sided alternatives (i.e. a two-sided p-value). If the boundaries are crossed for efficacy endpoints at any interim analyses, for any of the aims, the study will continue. If the boundaries are crossed in Specific Aims 2-4, the primary specific aim, whether Vitamin D supplementation in pregnancy is associated with a reduction in asthma and/or recurrent wheeze risk, still needs to be assessed, thus the study should continue to monitor this endpoint. If the boundaries are crossed during an interim analysis of the primary aim, the study will also be continued, as the target intervention period (i.e., pregnancy) will have passed for all recruited subjects, and will feel that it is most important to examine the impact of this intervention on the children at 3 years of age. If the study is stopped early due to the success of the intervention, important clinical and outcome information may be lost. Therefore, we feel that it is important to continue the study even if interim analysis boundaries are crossed. The only situation when consideration will be given to prematurely stopping the trial will be for safety considerations. It is inevitable that adverse health events will be observed in all contexts noted above even if both treatments have no biological effects whatsoever. If the rate of adverse events on the active arm substantially and persistently exceeds the rate on the control arm, even in the absence of biological theory that connects the adverse events to vitamin D exposures, and no evidence of therapeutic effect or benefit of the active treatment is apparent in interim analyses, then premature termination of the study may be considered on safety grounds. The DSMB will be asked to articulate

reasonable definitions of 'substantial and persistent excess' of adverse event rate if this situation emerges.

An IOM committee has been named to undertake a study to assess current relevant data and update as appropriate the Daily Reference Intakes (DRIs) for vitamin D and calcium. It is likely that the report from this committee (expected to be released in May, 2010 – 10 months into the recruitment phase; <http://iom.edu/?ID=61170>) will recommend a higher DRI for vitamin D (currently 200 IU/day for women of child-bearing age). This is one other concern regarding a potential cause for early study termination. If the IOM recommends Vitamin D supplementation of up to 2,000 IU/day during the course of the study, and if this increase in recommended supplementation occurs early in the course of the study (i.e., while the study is still in the antenatal monitoring phase), the likely target supplementation recommendation ( $\leq 2,000$  IU/day) is well below the supplementation level indicated for the treatment group in this study. Even if the 2,000 IU recommendation results in additional supplementation occurring in the placebo arm, there should still be a measurable difference in outcomes, with regard to maternal vitamin D levels. [name] previous trial had shown a statistically significant difference in 25(OH)D levels between the 2,400 IU/day and the 4,400 IU/day doses (Figure 1 in the VDAART Protocol). 25(OH)D levels will be available in the mothers to assess the impact of the IOM recommendation on the study outcomes. Consideration of increasing the dose in the intervention arm will be considered, after a meeting with the VDAART Trial Steering Committee, the NHLBI staff, and the DSMB. If an IOM recommended increase in supplementation occurs after the antenatal supplementation period, this will have little impact on any study outcome, as the crucial window of Vitamin D supplementation for the prevention of asthma occurs in the antenatal period. In the unlikely event of an IOM recommended increase in supplementation  $>2,000$  IU/day, a meeting between the VDAART Steering Committee, the NHLBI Staff, and the DSMB members will be convened to discuss potential alternative plans, including early termination of the trial.

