
Our primary aims are:

1. To determine whether vitamin D supplementation in the pregnant mother is associated with reduced incidence of asthma in the child during the first 3 years of life. Our primary outcomes will be doctor's diagnosis of asthma and/or recurrent wheeze in the child at age 3 years.

2. To determine whether a vitamin D dose of 4,400 IU per day vs. the standard 400 IU/day in pregnancy is sufficient to maintain mothers' vitamin D levels in the range of  $\geq 75$  nmol/L 25(OH)D.

In addition to our primary aims, we have the following secondary aims of the trial:

3. To determine whether vitamin D supplementation in the pregnant mother is associated with reduced secondary outcomes in the neonate of cord blood total IgE, and reduced secondary outcomes in the 3-yr old child of (a) allergic sensitization (total and specific IgE), (b) eosinophil count, (c) doctor's diagnosis of eczema and (d) lower respiratory tract infections.
4. To determine whether vitamin D supplementation in the pregnant mother is associated with improved vitamin D status in their offspring through measurement of 25(OH)D levels in cord blood (at delivery), and children's blood (at 1 and 3 yrs of age).
5. To determine whether sufficient vitamin D supplementation in the pregnant mother is associated with reduced incidence of preterm birth (birth <37 weeks gestation), preeclampsia, gestational hypertension, and/or Hemolytic anemia, Elevated Liver enzymes, Low Platelet count (HELLP syndrome) (PB/PE) compared to a usual care control group in VDAART.

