where the parameters are as defined in Specific Aim 1. The  $k$  measured covariates for these analyses will be environmental, maternal, and child factors specific to 25(OH)D levels, such as sun exposure behavior, dietary intake of Vitamin D, and ethnicity. Additionally, any relevant covariates from Table 9 demonstrating main effects that have biologically plausible interactions with Vitamin D supplementation will be tested for effect modification. For both models, it is assumed that  $\varepsilon_i \sim N(0, \sigma^2)$ . The hypothesis that  $\delta_k=0$  will be used to examine whether any of these factors predict 25(OH)D levels, and the results will be used to adjust for any distributional imbalances of these factors across Vitamin D supplementation groups. As with the previous specific aims, we will also tests for effect modification via the hypothesis that  $\eta_k=0$ , or whether any maternal, child, or demographic/environmental covariates modify the relationship between vitamin D intake and circulating 25(OH)D levels in mother's plasma or cord blood. Additionally, we will follow the guidelines outlined in Specific Aim 2 to obtain the most parsimonious model.

The hypothesis that 25(OH)D levels in the child's blood will be higher in the 4400 IU group at birth, age 1 and age 3 will be tested using a repeated measures analysis framework such as generalized estimating equations.

#### P.2.d. Plan for Specific Aim 5

This specific aim investigates whether sufficient vitamin D supplementation in the pregnant mother is associated with reduced incidence of preterm birth (birth <37 weeks gestation) and/or preeclampsia, gestational hypertension, and/or HELLP syndrome compared to a usual care control group in VDAART.

The hypothesis that the incidence of preterm birth/preeclampsia, gestational hypertension and HELLP syndrome (PB/PE) is reduced in the high-dose vitamin D supplementation will be tested using logistic regression, allowing for fixed effect of center. Additional analysis will consider the modification of vitamin D exposure effects by maternal demographic/behavioral factors such as maternal age, BMI and weight gain during pregnancy, and maternal history of asthma/allergy, race, and other factors potentially associated with preterm birth/preeclampsia, gestational hypertension, HELLP or vitamin D exposure.

Letting  $M_i$  be an indicator function for the primary endpoint, PB/PE, for the  $i^{\text{th}}$  subject, the model is:

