Based on the observed differences/variation in 25(OH)D levels, we used simulation studies to estimate the power to detect a mean difference of 7.5 – 37 nmol/L across the supplemented and control groups in maternal plasma at 26-28 weeks, as well as maternal plasma and cord blood at delivery, using an estimated standard deviation of 40. We anticipate that the difference in 25(OH)D levels in maternal plasma across treatment groups will be less

pronounced at the 26-28 week measurement period (e.g., 12.5 – 25 nmol/L), and we do not expect to observe a significant difference by supplementation status in circulating vitamin D in infants at 1 and 3 years of age, since no post-natal treatment intervention is planned. The simulations were generated in a similar manner to method described for Specific Aim 2, except that linear regression (rather than logistic) was used to model the relationship between circulating vitamin D and vitamin D supplementation status. Study heterogeneity was incorporated into the model by allowing 25(OH)D levels to vary by 25 nmol/L across study sites. Since this phenotype will be measured five times throughout the study period, the power was defined as the proportion of replicates with a Wald test statistic (i.e., testing the null hypothesis that the coefficient for vitamin D supplementation status is 0) 2-sided p-value was less than 0.01 (0.05/5). Additionally, this specific aim will include 2 interim and a final analysis, which will be identical to the procedure outlines for specific aim 2. While the power estimates below do not directly incorporate the interim looks, we feel that the power reduction will be modest. The results are shown in Table 7.

**Table 7. Power to detect a 7.5 – 37 nmol/L difference in 25(OH)D for 870 subjects in a multi-site study, (effectively 660 patients, assuming an 8% miscarriage rate and 18% loss to follow-up).**

| Mean change in 25(OH)D levels in 4400 IU group (nmol/L) | Power |
|---------------------------------------------------------|-------|
| 7.5                                                     | 0.444 |
| 12.5                                                    | 0.925 |
| 25                                                      | 0.999 |
| 37                                                      | 0.999 |

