#### L. Study Timeline

|               |             |                                                                                                                                            |
|---------------|-------------|--------------------------------------------------------------------------------------------------------------------------------------------|
| Year 1 | Months 0-4  | Planning and preparation
- Training of RAs
- Preparation of Study medications
- Printing of questionnaires                        |
|               | Month 6     | Screening and recruitment begins
Randomization and intervention                                                                         |
|               | Month 12    | First group of mothers deliver                                                                                                             |
| Year 2 | Month 3     | First group of quarterly calls for follow-up of infants begins                                                                             |
|               | Month 6     | Data clean up, interim analysis of SA2 and SA4                                                                                             |
|               | Month 11    | Last group of mothers screened, recruited, and randomized                                                                                  |
|               | Month 12    | First group of in-person visits for 1-yr old infants                                                                                       |
| Year 3 | Month 6     | Last group of mothers deliver
Data clean up, interim analysis of all specific aims                                                      |
|               | Months 6-12 | Quarterly follow-up calls and yearly in-person visits continue                                                                             |
| Year 4 | Month 1-5   | Quarterly follow-up calls and yearly in-person visits continue . Data clean up, interim analysis of all SA1/SA3, final analysis of SA2/SA4 |
|               | Months 6-12 | Quarterly follow-up calls and yearly in-person visits continue                                                                             |
| Year 5 | Months 1-5  | Quarterly follow-up calls and yearly in-person visits continue                                                                             |

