|               | Month 5     | First group of in-person visits for 3-yr old children                                                                                      |

|                          |             |                                                                                                                  |
|--------------------------|-------------|------------------------------------------------------------------------------------------------------------------|
|                          | Months 5-12 | Data clean up, interim analysis of all SA1/SA3
Quarterly follow-up calls and yearly in-person visits continue |
| No Cost Extension | Month 4     | Finish in-person visits for last group of 3-yr old children                                                      |
|                          | Months 5-10 | Finish data clean-up and statistical analyses                                                                    |
|                          |             | Manuscript preparation and presentation of findings                                                              |

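### The scheduled final analysis of Aim 4 (year 4 month 5) precedes all age-3 samples, and the child 25(OH)D analysis has no date or boundary of its own

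*Supplement*

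**What the plan says.** All references are to the current protocol.

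- **Aim (Section II).** Aim 4 concerns offspring vitamin D status, measured by "25(OH)D levels in cord blood (at delivery), and children's blood (at 1 and 3 yrs of age".
- **Analysis (P.2.d, Aim 4).** The hypothesis is that the child's level is higher in the 4400 IU arm; levels "at birth, age 1 and age 3 will be tested using a repeated measures analysis framework such as generalized estimating equations". No calendar date is given, and no arm-by-visit term is mentioned.
- **Multiplicity (P.3).** Five 25(OH)D analyses share a Bonferroni correction. Infant plasma at years 1 and 3 accounts for two of them. Q.4 uses two-sided 0.01.
- **Schedule (VII.K).** Aims 2 and 4 are described as delivery outcomes, meaning cord-blood and maternal levels. The stated plan is that "there will be two interim looks and a final analysis (year 2 month 5, year 3 month 5, and year 4 month 5, respectively". The boundaries are |z| = 3.7103, 2.5114 and 1.993. Only Aims 1 and 3 are given a final analysis at the end of the study.
- **Timeline (VII.L).** Year 4 months 1-5 lists "interim analysis of all SA1/SA3, final analysis of SA2/SA4", with no restriction to delivery measurements. Year 5 month 5 lists "First group of in-person visits for 3-yr old children". The interim analysis entered for later in Year 5 names Aims 1 and 3 only.
- **Expected result (Q.4).** "we do not expect to observe a significant difference by supplementation status in circulating vitamin D in infants at 1 and 3 years of age", because no post-natal intervention is planned.

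**The concern.** The same aim is given two scopes. Section II, P.2.d and P.3 run it to age 3. VII.K and VII.L give it a final analysis while the children are still too young. A team following the schedule would report Aim 4 as final without one of the two post-natal ages it names. The date, alpha and model for the remaining part would then be chosen after the maternal and cord-blood results were known.

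A second gap lies in the model. P.2.d names a framework but not the contrast of interest. Cord blood is expected to differ between arms and ages 1 and 3 are not. If one arm coefficient were fitted across the three time points, a difference present only at birth could be reported as improved status through age 3.

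**Working it through.** **1. The plan's own figures.** With 330 per arm, SD 40 and two-sided alpha 0.01 (Q.4), the standard error of a mean difference is 40 × √(2/330) = 3.11. Power is Φ(difference/3.11 − 2.576).

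| Difference (nmol/L) | Recomputed | Table 7 |
|---|---|---|
| 7.5 | 0.434 | 0.444 |
| 12.5 | 0.925 | 0.925 |
| 25 | >0.999 | 0.999 |
| 37 | >0.999 | 0.999 |

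The three-look boundaries also reproduce (3.7103, 2.5114, 1.9930) with equally spaced looks and overall two-sided 0.05. The sample size is consistent: 870 × 0.92 × 0.82 = 656, about 660. The plan's numbers are sound; the problem is one of timing and scope.

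**2. Calendar.** Study month = 12 × (year − 1) + month. Dates are from VII.L and VII.K.

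| Event | Stated | Study month |
|---|---|---|
| First deliveries | Year 1 month 12 | 12 |
| Last deliveries | Year 3 month 6 | 30 |
| Aim 4 final analysis | Year 4 month 5 | 41 |
| First age-3 visits | Year 5 month 5 | 53 |
| Last age-3 visits | No Cost Extension month 4 | 64 |

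- Oldest child at the final analysis: 41 − 12 = 29 months.
- Youngest child: 41 − 30 = 11 months.
- Earliest third birthday: 12 + 36 = month 48, which is 7 months after the final analysis. The listed first age-3 visit is 53 − 41 = 12 months after it.
- Age-3 samples available: 0 of about 660.
- Age-1 data: if births are spread evenly over months 12 to 30 (an assumption), (41 − 12 − 12)/(30 − 12) = 17/18, or about 94%, have turned 1.

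Even a child born when recruitment opened (month 6) would be only 35 months old. The listed age-3 visits (months 53 to 64) do not match third birthdays exactly (months 48 to 66), but this does not affect the result.

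**3. Threshold.** The final boundary |z| = 1.993 corresponds to two-sided p = 0.046. P.3 and Q.4 point to 0.01. Nothing says which applies to a child analysis run after the look labelled final.

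**4. Illustration of the model gap.** This applies only if a single common arm coefficient is fitted over three equally weighted visits, there is no difference at ages 1 and 3, and the within-child correlation ρ is assumed, since the protocol gives none. The pooled effect is D/3, where D is the cord-blood difference. Its standard error is 40 × √((1 + 2ρ)/3) × √(2/330).

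- D = 35 nmol/L (the maternal difference cited in Q.4, which the protocol also uses to set its cord-blood expectation): pooled effect 11.7. At ρ = 0.3 the standard error is 2.27, and the chance of p < 0.01 is Φ(11.67/2.27 − 2.576), about 99.5%. For ρ from 0 to 0.5 the range is 98-100%.
- D = 12.5 nmol/L: pooled effect 4.2 and power of 17-40% over the same range of ρ, against 92.5% in Table 7 for one time point.

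Under that model a cord-only effect would almost surely give a significant coefficient at D = 35, and a smaller cord effect would be diluted.

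**The case against.** A reader might infer that the age-3 part of Aim 4 cannot be answered. The documents do not support that. Section VI.F still collects child blood at 3 years. VII.K continues the study even if a boundary is crossed. VII.L has a period for completing statistical analyses in No Cost Extension months 5-10, after the last age-3 visits and not tied to any aim. VII.K also ties its schedule to maternal and cord blood, so it can be read as dating the delivery part and saying nothing about the child part. P.2.d makes a similar split between immediate and long-term impact. This stands, and it confines the point to a gap in the schedule.

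It does not remove the gap. VII.L puts the final analysis of Aim 4 in Year 4 without restriction, and VII.K gives a study-end analysis to Aims 1 and 3 only. The spending-function flexibility in VII.K concerns interim looks; it does not date a child analysis after the last of three boundaries that together use the full 0.05.

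Two other inferences also go too far. Bonferroni shares are not lost by testing ages 1 and 3 later, since each comparison keeps 0.01 whenever it is run. Nor does the protocol commit to one pooled coefficient: P.2.d gives only an example framework, and P.3 counts separate analyses, which argues against pooling. Stating the hypothesis as higher at every age while expecting no difference later is openly disclosed in Q.4, and P.3 makes all tests two-sided.

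**Conclusion.** The inconsistency is real and modest. Followed literally, the Aim 4 final analysis contains no age-3 data and incomplete age-1 data (about 94% of children past their first birthday, if births are evenly spread), and the child analysis has no date or boundary elsewhere. The calendar result rests only on dates in VII.K and VII.L. The model point is a request for specification: the pooled figures are conditional on a single arm coefficient and an assumed correlation, and do not describe an analysis that the plan states. The primary outcome is unaffected, and the protocol itself expects no significant child difference at ages 1 and 3.

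**What to change.** - **VII.K and VII.L.** State that year 4 month 5 and its three-look boundary are final only for maternal and cord-blood 25(OH)D. State that child 25(OH)D at ages 1 and 3 is analysed at study end, alongside Aims 1 and 3, at its Bonferroni level of 0.01.
- **P.2.d (Aim 4).** Specify arm-by-visit terms and base conclusions on the contrast at each visit. Say that ages 1 and 3 assess carry-over, where Q.4 expects no significant difference.

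The cost is wording in three sections and later reporting of the child part. No visit or sample is added. Table 7 power per time point is unchanged, because it already assumes the 660 children left after three-year losses and alpha 0.01.

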### P.3 Multiple comparisons.

All pre-specified hypotheses will be tested individually at the 0.05 level of significance, using a conservative two-sided alternative hypothesis (even when the stated hypothesis is one-sided). More specifically, the primary and secondary hypotheses of Vitamin D supplementation and Asthma/Recurrent Wheeze, Allergy/Eczema/LRI, will not be adjusted for multiple comparisons, since they have been defined a priori and are limited in scope. Additionally, an interim analysis plan has been developed for the primary outcome to adjust for the number of times (3) asthma and/or recurrent wheeze will be analyzed over the study period. Since 25(OH)D status is being examined in 5 separate analyses (maternal plasma at 26-28 weeks, maternal plasma at delivery, cord blood at delivery, infant plasma at years 1 and 3), this analysis will be adjusted for 5 multiple comparisons (i.e., using Bonferroni correction). Finally, any findings with respect to interaction terms (i.e., exploring whether environmental and demographic covariates affect the relationship between Vitamin D supplementation and the outcome of interest) for any of the hypotheses will be adjusted (i.e., using FDR methodology) for the number of models tested, and interaction testing will be limited to those defined in sections D.14.2a-c, in order to limit the potential for spurious findings. Any serendipitous findings coming from exploratory analyses will be clearly reported as such, and test statistic p-values will be adjusted by the number of exploratory hypotheses considered (using FDR or another appropriate procedure for multiple comparisons adjustment).

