**Q.2. Power for Specific Aim 2.** We expect that there will be 400 women in each arm for this analysis due to the 8% miscarriage rate. We do not expect there to be significant LTF by delivery. Like the analysis plan for Specific Aim 1, we plan to incorporate interim analyses, using a Lan-Demets spending function with O'Brien-Fleming type bounds. For this specific aim, we plan for three looks, which results in stopping boundaries of  $|z|=3.7103$ , 2.5114, and 1.993, for the first, second, and final analysis, respectively. As above, the thresholds will be adjusted if the recruitment varies from the expected targets. As shown in Table 5 below, we will have excellent power to detect an increase of 20-60% in the proportion of mothers with 25(OH)D levels > 75 nmol/L between the intervention and the control group. The power calculations did not explicitly account for the interim analyses, however, the power should still be >0.999 even after distributing the alpha level across multiple looks.

**Table 5. Power to detect a 20-60% absolute increase in the proportion of mother's with 25(OH)D > 75 nmol/L for 800 patients in a multi-site study\***

| Proportion of mothers with 25(OH)D > 75 nmol/L in 400 IU group | Proportion of mothers with 25(OH)D > 75 nmol/L in 4400 IU group |            |            |
|--------------------------------------------------------------------------|---------------------------------------------------------------------------|------------|------------|
|                                                                          | 90%                                                                | 80% | 70% |
| 0.50                                                              | >0.999                                                                    | >0.999     | >0.999     |
| 0.40                                                              | >0.999                                                                    | >0.999     | >0.999     |
| 0.30                                                              | >0.999                                                                    | >0.999     | >0.999     |

\* 8% miscarriage rate

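### Aim 4's 25(OH)D tests carry two significance levels: Bonferroni 0.01 in P.3 and Q.4, but sequential boundaries in VII.K that spend 0.05 on each comparison

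*Supplement*

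**What the plan says.** All references are to the current protocol and the addendum to its analysis plan.

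- **P.3, Multiple comparisons.** The general rule is "All pre-specified hypotheses will be tested individually at the 0.05 level of significance". The 25(OH)D analyses are an exception: "this analysis will be adjusted for 5 multiple comparisons (i.e., using Bonferroni correction"). The five are listed as "maternal plasma at 26-28 weeks, maternal plasma at delivery, cord blood at delivery, infant plasma at years 1 and 3".
- **Q.4, Power for Specific Aim 4.** Power is the share of simulated trials in which the "2-sided p-value was less than 0.01 (0.05/5"). The same paragraph adds: "Additionally, this specific aim will include 2 interim and a final analysis, which will be identical to the procedure outlines for specific aim 2". It says that Table 7 does not directly incorporate the interim looks.
- **Q.2, Power for Specific Aim 2.** The Aim 2 procedure is a Lan-DeMets spending function with O'Brien-Fleming-type bounds. The boundaries are |z| = 3.7103, "2.5114, and 1.993, for the first, second, and final analysis, respectively".
- **VII.K, Interim Analyses.** Aims 2 and 4 share those values: "For the second and fourth specific aim, with 3 looks in total, the crossing boundaries are" 3.7103, 2.5114 and 1.993. VII.K describes the outcomes under these looks as the ones monitored at delivery, namely maternal and cord-blood 25(OH)D. The final look is at year 4 month 5.

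No section recomputes the boundaries for Aim 4 at 0.01 or says how the Bonferroni correction and the sequential bounds work together. The addendum is silent on it.

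**The concern.** Two sections each supply a decision rule for the same tests, and the rules disagree. If the VII.K boundaries decide, each Aim 4 comparison is tested at an overall 0.05, and the Bonferroni protection promised in P.3 is lost for those comparisons. If P.3 decides, the VII.K boundaries are wrong for Aim 4. A result in the gap could be reported as positive or negative depending on the section cited. Table 7's power also belongs to a threshold that VII.K does not use.

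**Working it through.** **Inputs.** Spending function, boundaries and three looks: Q.2 and VII.K. Bonferroni level 0.05/5 = 0.01: P.3 and Q.4. SD 40 nmol/L, 660 analysed: Q.4 and Table 7. About 330 per arm: P.1. Equal spacing of the looks is an assumption, and step 1 supports it.

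**1. Reproduce the stated boundaries.** The cumulative two-sided alpha spent at information fraction t is 4 × [1 − Φ(z₁₋α/₄ / √t)]. With α = 0.05 and t = 1/3, 2/3 and 1, this is 0.0002, 0.0121 and 0.0500. Solving for the bounds by recursive integration gives 3.7103, 2.5114 and 1.9931, which are the protocol's values. They are correct for one test at 0.05. Their nominal two-sided p-values are 0.0002, 0.0120 and 0.0463, so even the second-look bound is looser than 0.01.

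**2. Boundaries at the Bonferroni level.** The same function and looks with α = 0.01 give 4.72, 3.25 and 2.59 (final nominal p about 0.0096).

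**3. Which level Table 7 uses.** SE = 40 × √(2/330) = 3.11 nmol/L, and power ≈ Φ(δ/SE − z).

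| Difference | Table 7 | Single test at 0.01 (z = 2.576) | Single test at 0.05 (z = 1.960) | Final look at 2.59 |
|---|---|---|---|---|
| 7.5 nmol/L | 0.444 | 0.433 | 0.673 | 0.428 |
| 12.5 nmol/L | 0.925 | 0.925 | 0.980 | 0.923 |

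Table 7 fits 0.01 and does not fit 0.05.

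**4. The zone of disagreement.** At the final look it runs from 1.993 × 3.11 = 6.2 nmol/L to 2.59 × 3.11 = 8.1 nmol/L. With the 400 per arm that Q.2 expects at delivery, SE = 40 × √(2/400) = 2.83 and the zone is 5.6 to 7.3 nmol/L. Q.4's expected maternal difference of 35 nmol/L gives z = 35/3.11 ≈ 11. Even 12.5 nmol/L, the low end of the range Q.4 anticipates in mid-pregnancy, gives z ≈ 4.

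**5. Family-wise error.** For the two comparisons that VII.K covers (maternal and cord), at 0.05 each under the null, it is 1 − 0.95² = 9.75% if they are independent. Simulating the three looks gives 8.8% at a correlation of 0.6 and 7.9% at 0.8. P.3 promises at most 5% for the whole family. At 0.01 each, these two would use at most 2%.

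**The case against.** **P.3 may simply stand on top of VII.K.** P.3 is the multiplicity section, and Q.4 repeats 0.05/5 in the paragraph that introduces the looks. One can fairly read 0.01 as the governing level, with the sequential layer not yet worked through. That stands in part: this is an unreconciled contradiction, and loss of control follows only if VII.K is the decision rule. But the text never says that P.3 overrides the bounds it gives to Aim 4 by name. Requiring 2.576 only at the end, while keeping 3.7103 and 2.5114 at the interim looks, would still spend about 0.018 per comparison. Q.2's promise to adjust thresholds concerns recruitment, not multiplicity.

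**The study continues after any crossing.** True, but continuing does not alter the final bound of 1.993.

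**A larger error.** A reader might apply 1.993 to all five comparisons and infer a family-wise error near 23% (1 − 0.95⁵). A reader might also place the main risk in the child's levels at ages 1 and 3, where Q.4 expects no significant difference. The documents do not support either reading. VII.K limits these looks to maternal and cord levels. In VII.L the final Aim 2/4 analysis falls in year 4 months 1–5, while the first 3-year visits come in year 5 month 5. The last deliveries are in year 3 month 6, so the 1-year samples are not complete by that look either. P.2.d analyses the child's levels in a repeated-measures model. The only error rate stated for them is P.3's.

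**The count of five is out of date.** Correct. Table 2 and VI.F show no maternal draw at 26–28 weeks or at delivery; the maternal draws are at enrollment, at 32–38 weeks and 1 year after delivery. Leftover text in VII.A and VIII still mentions one at delivery. This adds to what must be repaired and does not remove the conflict.

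**Conclusion.** The contradiction holds. As written, the Aim 4 boundaries spend five times the alpha that P.3 and Q.4 allot to each comparison. For maternal and cord levels, a final |z| between 1.993 and about 2.59 has opposite verdicts in the two places, and the family-wise error over those two comparisons is up to about 10%. This rests on equally spaced looks, on VII.K's bounds being the decision rule, and, for the nmol/L zone, on SD 40 and 330 per arm.

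The practical weight is moderate. Aim 4 is secondary, the treatment raises the quantity being measured, and the expected maternal difference is about 11 standard errors, so a changed maternal conclusion is unlikely. The point should be corrected, but it does not threaten the trial's main result.

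**What to change.** - In VII.K, take Aim 4 out of the sentence with 3.7103, 2.5114 and 1.993, and in Q.4 drop the statement that its procedure is identical to Aim 2's. Give Aim 4 its own boundaries at the Bonferroni level: 4.72, 3.25 and 2.59 for 0.01 and three equally spaced looks. Alternatively, test each comparison once at |z| = 2.576.
- In P.3, replace the list of five with the comparisons the current sampling schedule supports, and say whether the maternal level is in that family (Section II makes it part of a primary aim; P.1 calls it a secondary outcome). If the count changes, recompute the divisor and the boundaries; four comparisons, for example, would give 0.05/4 = 0.0125.
- State that the child's levels are tested at the same Bonferroni level, outside the sequential looks.

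The cost is wording, three boundary values and a slightly stricter Aim 4 threshold. Final-look power stays about 0.43 at 7.5 nmol/L and 0.92 at 12.5 nmol/L, because Table 7 was already computed at 0.01.
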